**Improbable:**

- A clinical event, including anomalous laboratory test findings, with a time relation to administration of the drug which makes a causal association unlikely, and where other drugs, chemical substances or intercurrent disease afford plausible explanations for the observed event.

**Unrelated:**

- None of the above criteria are met.

#### **9.4.4 Duration**

For both AEs and SAEs, the Investigator will provide a record of the start and stop dates of the event.

#### **9.4.5 Action Taken**

The Investigator will report the action taken with IMP as a result of an AE or SAE, as applicable (e.g., discontinuation or reduction of IMP, as appropriate) and report if concomitant and/or additional treatments were given for the event.

#### **9.4.6 Outcome**

SAE will be followed preferably until:

- Resolution of the event;
- Stabilization of the event; or
- Resetting the baseline situation of the event, in case baseline situation is available.

Otherwise, they will continue until:

- The event can be attributed to products other than the study medication or factors unrelated to the study; or
- It is unlikely to obtain further information.

## 9.5 ABNORMAL LABORATORY VALUES

An abnormal laboratory value is considered to be an AE if the abnormality:

- results in discontinuation from the study;
- requires treatment, modification/ interruption of IP dose, or any other therapeutic intervention; or
- is judged to be of significant clinical importance.

Regardless of severity grade, only laboratory abnormalities that fulfill a seriousness criterion need to be documented as a serious adverse event.

If a laboratory abnormality is one component of a diagnosis or syndrome, then only the diagnosis or syndrome should be recorded on the AE page/screen of the CRF. If the abnormality was not a part of a diagnosis or syndrome, then the laboratory abnormality should be recorded as the AE.

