## 5.3 ENDPOINTS

### 5.3.1 Primary endpoint(s)

1. Safety and tolerability evaluation as measured by  $\geq 3$  grade adverse events (AE) and serious adverse events (SAE).
2. Reduction of the viral reservoir measured in CD4+ T cells by digital droplet PCR (ddPCR) at baseline and 1 week after 3rd dose of RMD (total HIV-1 DNA copies per  $10^6$  CD4+ T cells)

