### 8.4.4 Vaccine patient diary

Data on local and systemic events will be solicited with specific diary cards (attachement F) for a minimum of 7 days following each immunization. Following parameters will be collected:

Local Reactogenicity, including:

- Redness (mm)
- Induration (mm)
- Pain (0-4)

General Symptoms, including:

- Temperature (°C)
- Headache (0-4)
- Fatigue (0-4)
- Nausea (0-4)
- Vomiting (0-4)
- Diarrhea (0-4)
- Abdominal pain (0-4)
- Sudoration (0-4)
- Muscular pain (0-4)
- Lack of appetite (0-4)
- Other, describe

0-4 grades intensity, according to the following definitions described at DAIDS:

- 0: No symptoms
- 1: Symptoms causing no or minimal interference with usual social & functional activities.

- 2: Symptoms causing greater than minimal interference with usual social & functional activities
- 3: Symptoms causing inability to perform usual social & functional activities
- 4: Symptoms causing inability to perform basic self-care functions OR Medical or operative intervention indicated to prevent permanent impairment, persistent disability, or death

The investigator will review the patient diary and ensure that proper record has been performed. The severity of each AE will be graded by the investigator. Criteria for grading clinical and laboratory events were based on DAIDS grading table. The investigator will state the relationship of each AE to the vaccination by using prespecified terms including unrelated, unlikely to be, possibly, probably and definitely related to vaccination. In those cases where grading of AE do not coincide with patient's description, a discussion will be registered in the medical record.

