### 9.2 MONITORING, RECORDING AND REPORTING OF ADVERSE EVENTS

An AE is any noxious, unintended, or untoward medical occurrence that may appear or worsen in a subject during the course of a study. It may be a new intercurrent illness, a worsening concomitant illness, an injury, or any concomitant impairment of the subject's health, including laboratory test values (as specified by the criteria below), regardless of etiology. Any worsening (i.e., any clinically significant adverse change in the frequency or intensity of a pre-existing condition) should be considered an AE. A diagnosis or syndrome should be recorded on the AE page of the CRF rather than the individual signs or symptoms of the diagnosis or syndrome.

An overdose, accidental or intentional, whether or not it is associated with an AE, or abuse, withdrawal, sensitivity or toxicity to an investigational product should be reported as an AE. If an overdose is associated with an AE, the overdose and AE should be reported as separate terms.

All subjects will be monitored for AEs during the study. Assessments may include monitoring of any or all of the following parameters: the subject's clinical symptoms, laboratory, pathological, radiological or surgical findings, physical examination findings, or other appropriate tests and procedures.

All AEs will be recorded by the Investigator from the time the subject signs informed consent until the last study visit or to 28 days after the last dose of IMP in case of early withdrawal while patient is receiving IMP. AEs and SAEs will be recorded on the AE page of the CRF and in the subject's source documents. All SAEs must be reported to the Sponsor (see contact details at the end of the paragraph) within 24 hours of the Investigator's knowledge of the event by facsimile, or other appropriate method, using the SAE Report Form (attachment N, can be found in the Investigator's File), or approved equivalent form.

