## 10 STATISTICS

The primary safety and tolerability analysis will include a description and summary of the number and percentage of grade  $\geq 3$  AE and SAE; their grading and imputability for both MVA.HIVconsV and RMD administrations.

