### 10.3 SAMPLE SIZE DESCRIPTION

Individuals that participated in the BCN01 trial and which are followed in the extension phase (BCN01-RO) will be offered to participate in the study. Therefore, the trial will enroll a maximum number of 24 subjects. The primary endpoint of the study is safety and tolerability of the combined kick & kill strategy in recently HIV-1-infected individuals under early suppressive therapy. In terms of total number of individuals exposed to each MVA.HIVcons vaccine and confidence intervals to detect an AE (i-e- based on published results the probability of experiencing a grade 3 or 4 AE is thought to be <0.1). Information on expected rates of AEs related to RMD at the clinical dose proposed is still scarce. The trial has been designed as a pilot study and will only allow detection of a large effect among participants. However, the incidence of grade  $\geq 3$  or SAEs will be used as a measure of safety of the experimental strategy.

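### A grade 3 or 4 laboratory value enters the primary safety count only if it is acted on or judged important, so the count can miss graded laboratory toxicity

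*Protocol*

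**What the plan says.** Section 5.3.1 gives the first primary endpoint as "Safety and tolerability evaluation as measured by" grade 3 or higher events, specifically "grade adverse events (AE) and serious adverse events (SAE"). Section 10 makes the analysis descriptive: "The primary safety and tolerability analysis will include a description and summary of the number and percentage of grade" 3 or higher adverse events and serious adverse events. Section 10.3 adds that their incidence "will be used as a measure of safety of the experimental strategy".

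Whether a laboratory result is an adverse event is settled in two steps. Section 9.2 brings laboratory findings into the definition, "including laboratory test values (as specified by the criteria below), regardless of etiology". Section 9.5 then supplies the criteria: "An abnormal laboratory value is considered to be an AE if the abnormality" causes withdrawal from the study, calls for treatment, a change to the product dose or another intervention, or "is judged to be of significant clinical importance". The three are alternatives, and none is a severity grade. Section 9.5 also says that grade by itself does not make a laboratory abnormality serious.

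On grading, section 8.4.4 states: "Criteria for grading clinical and laboratory events were based on DAIDS grading table". Section 8.4.5 says much the same for romidepsin.

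**The concern.** The endpoint is defined by grade, but for laboratory findings the way into it is action or judgement. A result can be grade 3 or 4 on the protocol's own scale and still not be counted, because it was never an adverse event.

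This matters more here than in many trials. Section 6.3.1 describes romidepsin as cytotoxic. Section 7.3.2 lists haematology and biochemistry values among the reasons to withhold it. Section 10.3 says that little is known about event rates at the dose used, so estimating them is a main purpose of the study. Sections 5.1 and 5.4.3 make the trial single-arm and open, and section 9.4 has investigators evaluate the events. With no comparator, an omission is not offset by a similar omission in another arm; it can only lower the reported rate.

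**Working it through.** **Tracing the rule.** The protocol gives no formula-based safety figure to reproduce: 24 is the size of the parent cohort, stated in section 10.3 as a maximum. The check is therefore one of definitions.

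1. Counted in the primary analysis: grade ≥3 adverse events and serious adverse events (sections 5.3.1 and 10).
2. A laboratory value is an adverse event only if it meets a criterion in section 9.5 (through section 9.2).
3. Grade is not among those criteria, and grade alone does not confer seriousness.
4. So a grade 3 or 4 value with no withdrawal, no intervention or dose change, and no judgement of importance enters neither half of the endpoint.
5. One side route exists. If the abnormality belongs to a diagnosis, section 9.5 has the diagnosis recorded instead, and it counts under the diagnosis's own grade.
6. No section requires every grade ≥3 laboratory value to be recorded as an adverse event or tabulated by grade.

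**How far the dosing limits close the gap.** Sections 7.3.1 and 7.3.2 speak of clinically significant laboratory abnormalities as a form of adverse event and point to a list of numeric limits. Acting on a limit by delaying or stopping a dose also meets the second criterion of section 9.5. Set against the laboratory panel and the calendar:

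| Situation | Covered by the limits? |
|---|---|
| Haemoglobin, neutrophils, lymphocytes, platelets, creatinine, AST, ALT, with a dose still to give | Largely, although the wording permits rather than requires delay or discontinuation |
| Creatine kinase, bilirubin, electrolytes (measured under section 8.4.2) | No limit listed |
| Abnormal 3 days or 1 week after the third infusion (weeks 5 to 6), normal again by the week 9 vaccination | No dose is changed |
| Any value after the week 9 vaccination (draws at weeks 10, 13, 17 and later) | No study dose remains to withhold |

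**Size of one omission.** At the maximum enrolment, 1/24 = 0.0417, or 4.2 percentage points per participant left out.

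**Precision at this size (exact two-sided 95% intervals).**

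- 0/24: 0% (0 to 14.2)
- 1/24: 4.2% (0.1 to 21.1)
- 3/24: 12.5% (2.7 to 32.4)

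**Illustration only.** Let p be the true proportion of participants with a grade ≥3 event and c the share of them who pass the section 9.5 criteria. The protocol gives no value for c, so the range is assumed. The expected number counted is 24 × p × c, and the chance of counting at least one is 1 − (1 − pc)^24. With p = 0.10 as an assumed value:

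| c | Expected number counted | Chance of at least one |
|---|---|---|
| 1 | 2.4 | 0.920 |
| 0.75 | 1.8 | 0.846 |
| 0.5 | 1.2 | 0.708 |
| 0.25 | 0.6 | 0.455 |

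The table shows how the reported figure depends on the share captured. It does not estimate that share.

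**The case against.** The strongest reply is that nothing here contradicts itself. Section 9.2 refers to criteria, section 9.5 gives them, and section 10 counts what results. A by-grade laboratory table is often left to a statistical analysis plan, which is not available here, and section 10 does not exclude one. The rule is indeed coherent, and the absence of such a table is not the complaint. The point is what the stated rule does to the primary figure: a separate laboratory listing elsewhere would leave that figure unchanged.

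The second reply is that discretion is limited. The limits in sections 7.3.1 and 7.3.2 give content to what counts as clinically significant, and sections 8.1.5, 8.1.7, 8.1.9 and 8.1.10 require laboratory results to be reviewed after each infusion. This stands for the seven listed parameters around dosing. A reader might infer that investigators are free to discard any grade 3 or 4 laboratory result; the document does not support that. The gap is the one in the table: unlisted analytes, values between doses or after the last one, and permissive wording. The DAIDS cut-offs are in Attachment O, which is not reproduced, so how often such values would arise cannot be judged.

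Third, a reader might infer that an undercount could carry the result across the expectation in section 10.3 that grade 3 or 4 events have probability below 0.1. That figure is an expectation from published results, in a sentence about the MVA vaccine, and not a decision threshold. The intervals for 1/24 and 3/24 both contain 10%, so moving between them changes no conclusion.

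**Conclusion.** The point holds as a limitation of the endpoint definition. Under sections 9.2 and 9.5, DAIDS grade alone does not bring a laboratory value into the primary grade ≥3 count, and the limits in sections 7.3.1 and 7.3.2 close the gap only in part. The primary safety figure can therefore undercount graded laboratory toxicity.

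The amount is unknown. The only size that follows from the protocol is 4.2 percentage points per omitted participant, assuming all 24 enrol; with fewer participants each omission weighs more. It would go too far to say that the figure is biased downwards as a matter of fact: that requires at least one uncounted grade ≥3 value, which the protocol cannot show in advance. Open label here means unblinded judgement of what counts. It does not mean differential bias, since there is no second arm.

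**What to change.** Leave section 9.5 unchanged for adverse event reporting. In section 10, state that the primary safety summary also gives:

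- the number and percentage of participants with a DAIDS grade ≥3 laboratory value that worsened from baseline, whether or not it was recorded as an adverse event;
- the combined number and percentage with either a grade ≥3 adverse event or such a laboratory value.

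Show both for two periods: from the first MVA vaccination to the start of the antiretroviral pause, and from the pause onwards. The split is needed because section 8.1.15 lists raised transaminases, lymphopenia and thrombocytopenia among the signs of acute retroviral syndrome. A single count over all follow-up would mix possible product toxicity with effects of viral rebound. The requirement of worsening keeps pre-existing abnormalities out.

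The cost is one more table, built from results already drawn at scheduled visits, and a reported rate that may look less favourable. No visit, dose or clinical rule changes.

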## 9.6 FEMALES OF CHILDBEARING POTENTIAL

Pregnancies and suspected pregnancies (including a positive pregnancy test regardless of age or disease state) of a female subject occurring while the subject is on romidepsin or MVA.HIVconsv, or within 28 days of the subject's last dose of romidepsin or MVA.HIVconsv, are considered immediately reportable events. Romidepsin or MVA.HIVconsv is to be discontinued immediately and the subject instructed to return any unused portion of romidepsin or MVA.HIVconsv to the Investigator. The pregnancy, suspected pregnancy, or positive pregnancy test must be reported to the Sponsor who, in case patient was exposed to romidepsin, will inform Celgene immediately using the Pregnancy Reporting Form provided by Celgene or an approved equivalent form.

Romidepsin may have reproductive toxicity if taken during pregnancy. In case the female subject was exposed to romidepsin, she should be referred to an obstetrician-gynecologist, preferably one experienced in reproductive toxicity for further evaluation and counseling.

The Investigator will follow the female subject until completion of the pregnancy, and must notify the Sponsor immediately about the outcome of the pregnancy (either normal or abnormal outcome).

If the outcome of the pregnancy was abnormal (e.g., spontaneous or therapeutic abortion), the Investigator should report the abnormal outcome as an AE. If the abnormal outcome meets any of the serious criteria, it must be reported as an SAE within 24 hours of the Investigator's knowledge of the event using the SAE Report Form, or approved equivalent form.

All neonatal deaths that occur within 28 days of birth should be reported, without regard to causality, as SAEs. In addition, any infant death after 28 days that the Investigator suspects is related to the in utero exposure to the IP should also be reported within 24

hours of the Investigator's knowledge of the event using the SAE Report Form, or approved equivalent form.

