### 7.2 EXCLUSION CRITERIA

1. Confirmed HIV-2 seropositive
2. Positive pregnancy test. \*
3. Presence of resistance drug mutations in the screening genotype \*\*
4. Participation in another clinical trial within 12 weeks of study entry
5. History of autoimmune disease other than HIV-related auto-immune disease.
6. History or clinical manifestations of any physical or psychiatric disorder which could impair the subject's ability to complete the study.
7. History of anaphylaxis or severe adverse reaction to vaccines.
8. Previous immunisation with any experimental immunogens (except for ChAd.HIVconsv and MVA.HIVconsv)
9. Receipt of blood products within 6 months of study entry
10. Treatment for cancer or lymphoproliferative disease within 1 year of study entry
11. Receipt of vaccines within 2 weeks of study entry and along the duration of the trial
12. Any other prior therapy which, in the opinion of the investigators, would make the individual unsuitable for the study or influence the results of the study

13. Current or recent use (within last 3 months) of interferon or systemic corticosteroids or other immunosuppressive agents

\* Female subjects of childbearing potential must not be pregnant, not be planning a pregnancy or breast-feeding. Sexually active women must be willing to use two approved methods of contraception (including condoms, diaphragm, spermicides, hormonal methods and/or intrauterine devices) from screening until 28 days after last immunization. Sexually active men in heterosexual relationships must be willing to use two approved method of contraception with their partners from screening until 28 days after last immunization.

\*\* Pre-cART genotype (performed at BCN01 screening visit)

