### 7.3.3 Related to cART interruption

As persistent detectable viral replication may induce immune activation that could favor a faster viral rebound after cART cessation, cART interruption will only be indicated if plasma viral load (pVL) is below the limit of detection in 2 consecutive determinations, spaced at least 1 week, at MAP visit (MVA2+8w). In case that MVA.HIVconsv second booster immunization may induce repetitive detectable plasma HIV-1 RNA determination still present at MAP visit, cART interruption will be postponed until 2 consecutive determinations are achieved.

Any individual for who is being considered for postponement of cART interruption will be discussed with the trial team.

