### 7.3.4 Early subject withdrawal

The patients will complete the clinical study before the stipulated time in the following circumstances:

- Concurrent process or illness which in the opinion of the investigator requires the withdrawal of the patient.
- Protocol deviation which in the opinion of the sponsor requires the withdrawal of the patient.
- The patient does not wish to continue in the study.
- Other

On the other side and in order to minimize risks of the treatment interruption intervention, an early interim and futility analyses is planned before the MAP phase for each individual. Treatment interruption would be discouraged if boosting MVA.HIVconsv is shown to be no longer immunogenic after romidepsin administration –defined as no net increase of HIVconsv-specific IFN $\gamma$  response compared to pre-vaccination levels with MVA.HIVconsv at BCN02-Romi baseline visit, due to RMD toxicity on CTL functional

activity for instance, as an improved viral control would not be foreseen. These results are considered valid for up to 12 weeks from the second vaccination. As vaccine induced T-cells may decrease in the following weeks and available data on expected kinetics of immune response is limited, in the event that the cART interruption is postponed more than MVA2 + 12w, the futility analyses should be repeated and results will be discussed among the investigators

In such situation, trial results would be focused on the viral reservoir and immunogenicity endpoints only until better correlates of control would be available to predict clinically relevant outcomes on which one could recommend treatment interruptions in a safer manner.

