#### 8.1.8 RMD3 – Third romidepsin infusion (week 5)

Before RMD3 visit, study physician will review lab test results from previous visit and will fill in the **romidepsin/ondansetron prescription**.

RMD3 visit will take place in UPIC (HTIP). Patients will be admitted in the morning (07:30am). Following procedures will be performed:

- Blood extraction including:
  - o Viral load, biochemistry (including Sodium, Potassium, Phosphate, Magnesium and Calcium), hematological parameters and CD4 count
  - o Plasma and PBMC storage following scheme detailed in attachment K (pre-RMD infusion, -4 hour time point of PK3)
- Urine pregnancy test
- Revision of romidepsin and ondansetron prescription
- Administration of ondansetron ev.
- Collection of romidepsin and ondansetron tablets from Pharmacy Service (already prepared by pharmacy personnel)
- Measurement of vital constants (pressure, temperature and cardiac frequency)
- Clinical visit by the investigator physician pre and post romidepsin infusion and revision of RMD diary card.
- Administration of romidepsin (4-hour infusion)
- Collection of PK3 samples (attachment K)
- Measurement of vital constants (blood pressure, temperature and cardiac rate) in the first 30 minutes after RMD infusion and within 30 minutes after RMD finalization
- Perform ECG within 30 minutes after RMD infusion to be reviewed by study physician.
- Fill in **RMD3 administration form** (attachment B).
- Provide the patient with the **RMD diary card** (attachment G).
- Give instructions to fill in the diary card / fill in together while admitted.
- cART adherence assessment (SERAD questionnaire)
- Both Study nurse and Study physician will monitor for appearance of clinical adverse events
- Give instructions to take ondansetron tablets. Provide patient with 6 ondansetron tablets. Take first ondansetron tablet while admitted.
- RMD3 + 3d visit scheduling

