#### **8.1.11 MVA2 – Second MVA vaccination and MVA1+9w – Nine weeks post MVA1 vaccination (week 9)**

Before MVA2 visit, study physician will review all vaccination criteria are met and will fill the **vaccination prescription form**.

MVA2 visit will take place in UPIC (HGTIP).

In MVA2 visit, as soon as patient arrives to UPIC, following procedures will be performed:

- Blood extraction including:
  - Plasma and PBMC storage following scheme detailed in attachment K
- Measurement of vital constants (blood pressure, temperature and cardiac rate)
- cART adherence assessment (SERAD questionnaire)
- Clinical visit including physical exam by the investigator physician pre and post vaccination
- Collection of MVA.HIVconsrv vaccine from the Pharmacy Service
- Preparation of MVA.HIVconsrv vaccine in the designated BL2 sterile hood located at IrsiCaixa following handling, thawing and preparation instructions detailed at the SOP (attachment I)
- Intramuscular administration of MVA.HIVconsrv vaccine in both deltoid muscles
- Measurement of vital constants 10 and 30 minutes after MVA injection.
- Fill in the **MVA.HIVconsrv administration form** (attachment C)
- Provide the patient with the **MVA diary card** (attachment F).
- Give instructions to fill in the diary card.
- MVA2+1w visit scheduling

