#### **8.1.14 MAP – Monitored antiretroviral pause and MVA2+8w – Eight weeks post MVA2 vaccination (17 weeks)**

Following procedures will be performed at both clinical sites (HGTIP and HC):

- Blood extraction including:
  - Viral load, biochemistry and hematological parameters.
  - Plasma and PBMC storage following scheme detailed in attachment K
- cART adherence assessment (SERAD questionnaire)
- Clinical visit, adverse event register
- Review acceptability for cART interruption after interim analyses (which will be performed at week 13 and be provided by investigational team in advance and recorded in 'Indication for MAP phase' form, attachment X)
- Review acceptability for cART interruption regarding plasma viral load suppression (pVL below the limit of detection in 2 consecutive determinations, spaced at least 1 week, and recorded in 'Indication for MAP phase' form, attachment X)
- Phase 2 study explanation including: cART interruption, site, weekly clinical visit, qualitative plasma viral load monitoring, criteria for cART resumption.
- CRF data collection

Once analytical results are available, cART interruption will be confirmed telephonically by study physician and first visit in BCN-Checkpoint will be scheduled.

In cases where pVL is not undetectable for 2 consecutive determinations, MAP will be postponed and extra visits will be scheduled (every week if pVL is 20-500 copies/mL, every two weeks if pVL is >500 copies/mL) including the following procedures until acceptability criteria for cART interruption are met.

- Blood extraction including:
  - Viral load, biochemistry and hematological parameters.
  - Plasma and PBMC storage.
- cART adherence assessment (SERAD questionnaire)
- Clinical visit, adverse event register

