### 8.1.15 MAP phase monitoring

Monitoring visits during the MAP phase will be performed at BCN-Checkpoint community center (see flow chart below). A specific MAP Phase Monitoring Form (attachment E) will be used to collect data.

During first 12 weeks post-MAP (from week 18 to week 29):

- Weekly visits will be performed, including:
  - o Clinical visit and adverse events register
  - o Reporting of symptoms suggestive of acute retroviral syndrome (including its severity grade):

|                                                  |                                                 |                                       |
|--------------------------------------------------|-------------------------------------------------|---------------------------------------|
|  Fever of unknown origin |  Headache               |  Pharyngitis  |
|  Lymphadenopathy         |  Transaminase elevation |  Lymphopenia  |
|  Oral candidiasis        |  Myalgia/arthralgia     |  Night sweats |

- |                                           |                                           |                                              |
|-------------------------------------------|-------------------------------------------|----------------------------------------------|
|  Fatigue          |  Nausea, vomiting |  Hepato/splenomegaly |
|  Rash             |  Diarrhea         |  Others              |
|  Trombochytopenia |                                           |                                              |

- 5ml blood extraction for :
  - Qualitative viral load test (Xpert HIV-1 Qual de Cepheid)
- Discussion on treatment resumption: recommendation on cART resumption will be assessed based on clinical visit, willingness of patients to resume treatment and detection of viral load in the qualitative test.
- Schedule of next appointment.
- Visits at 2, 4, 8, and 12 weeks after treatment interruptions (weeks 19, 21, 25 and 29) will also include
  - Biochemistry and hematological parameters, viral load and CD4 count (performed at an external Lab)

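### Required contraception and pregnancy reporting end at nominal week 13, at least four weeks before cART is paused, and the body text names pregnancy neither for starting the pause nor for restarting cART

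*Protocol*

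**What the plan says.** **Safeguards.** In Protocol 9.6, pregnancies on product or within 28 days of the "last dose of romidepsin or MVA.HIVconsv, are considered immediately reportable events"; the investigator then follows the woman to the end of the pregnancy and notifies the outcome. The 7.2 footnote requires two contraceptive methods, ending thus: "hormonal methods and/or intrauterine devices) from screening until 28 days after last immunization". Men in heterosexual relationships have the same end date.

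**Calendar.** Romidepsin is given at weeks 3, 4 and 5 (6.3.1) and MVA.HIVconsv at weeks 0 and 9 (6.3.2). The pause is offered at week 17, eight weeks after MVA2 (5.2, 8.1.14). It is postponed while viral load stays detectable.

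**Criteria.** Sections 7.3.1 and 7.3.2 each list pregnancy as a reason to stop the product. Section 7.3.3 says "cART interruption will only be indicated if plasma viral load (pVL) is below the limit of detection in 2 consecutive determinations". Section 8.1.14 has two checks: the interim immunogenicity result, and "Review acceptability for cART interruption regarding plasma viral load suppression". During the pause (8.1.15), "recommendation on cART resumption will be assessed based on clinical visit, willingness of patients to resume treatment", together with the qualitative test and, at some visits, a CD4 drop. Section 8.1.16 adds rules based on viral load, symptoms, laboratory abnormalities and CD4.

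**Testing.** The visit descriptions list pregnancy tests at screening and at each romidepsin visit. The last is the "Urine pregnancy test" at RMD3, week 5 (8.1.8). Before MVA2 the "study physician will review all vaccination criteria are met and will fill the" prescription form (8.1.11). That review takes in pregnancy through 7.3.1, but no test is listed at the visit.

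**The concern.** The safeguards follow exposure to the two products. This trial adds a second exposure, time without antiretroviral treatment and possibly with viraemia, and it begins after the safeguards have ended.

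A woman may conceive between week 13 and the pause, or during the pause. In the body text no immediate-reporting or follow-to-outcome duty then applies. No stated criterion keeps her from starting the pause, and none directs a restart. One branch of 8.1.16 leans the other way. After a positive qualitative test (indicative of more than 200 copies/mL, 8.1.15), if the confirmatory viral load is below 2,000 and there are no symptoms, laboratory abnormalities or significant CD4 drop, cART stays off. That branch has no exception for pregnancy. What is at stake is the safety of the participant and the fetus, not the analysis.

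**Working it through.** **1. The plan's own figure.** MVA2 week 9 + 8 weeks = week 17, which matches 5.2 and 8.1.14.

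**2. End of cover.** Romidepsin: week 5 + 28/7 = week 9. MVA2: week 9 + 28/7 = week 13. The later date governs, so both windows end at week 13.

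**3. Gap to the pause.**
- On schedule: 17 − 13 = 4 weeks.
- The pause is timed from MVA2. If MVA2 falls at week v, the gap is (v + 8) − (v + 4) = 4 weeks, so delaying MVA2 does not close it.
- Pause postponed to MVA2+12w (week 21): 21 − 13 = 8 weeks.

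Visit windows, which attachment J may set, could shift these by days.

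**4. Age of the last check when the pause starts.** Criteria review at week 9: 17 − 9 = 8 weeks. Last listed test at week 5: 17 − 5 = 12 weeks.

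**5. Time off cART without cover.** For a participant who rebounds and restarts on the 8.1.16 schedule, this is the day of the first positive test plus 7 to 10 days.

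| First positive | Days off cART |
|---|---|
| Pause week 1 | 7 + 7 to 10 = 14–17 |
| Pause week 4 | 28 + 7 to 10 = 35–38 |
| Pause week 12 | 84 + 7 to 10 = 91–94 |

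Those who do not rebound stay off longer.

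**6. Reach of general AE recording.** Recording runs to the last visit (9.2), which is 24 weeks after restart (8.2.1). With the first positive at pause week m and restart one week later, that visit falls at week 17 + m + 1 + 24 = 42 + m. For m = 12 this is week 54, which agrees with the follow-up in 7.1. A pregnancy that begins on the first day of the pause is then observed for (42 + m) − 17 = 25 + m weeks: 26 weeks for m = 1, 29 for m = 4 and 37 for m = 12. One that begins later in the pause is observed for less.

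**7. Criteria side by side.**

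| Decision | Section | Pregnancy named? |
|---|---|---|
| Stop vaccination | 7.3.1 | Yes |
| Stop romidepsin | 7.3.2 | Yes |
| Start the pause | 7.3.3, 7.3.4, 8.1.14, 10.2 | No |
| Restart cART | 8.1.15, 8.1.16 | No |

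**The case against.** The strongest reply is that the body text hands operative detail to attachments that are not shown: J (schedule of procedures), M (pause decisions), X (indication for the pause), AB (interruption decision chart) and N (pregnancy notification). Any of these may add a test or a criterion. This stands for the criteria and the testing. It does not remove the two windows, because 9.6 and 7.2 state them outright; an attachment with a longer window would contradict them.

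Second, both windows suit product exposure and agree with each other, and the pause is not a product. That is true, but it explains the gap without closing it.

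Third, other routes exist. Women planning a pregnancy are excluded at entry. Clinical visits are weekly and then fortnightly during the pause, and restart may follow from the clinical visit or the patient's wish. Section 7.3.4 allows withdrawal for a "Concurrent process or illness which in the opinion of the investigator requires the withdrawal of the patient". These routes permit protective action. None directs it, and none extends either window.

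A reader might infer that 8.1.16 obliges a pregnant participant to stay off cART. The document does not support that: the branch sits within a discussion of resumption, and the routes above remain open. A reader might also infer that a pregnancy during the pause would go unrecorded. That too goes too far: AEs and SAEs, with congenital anomaly among the SAE criteria, are recorded to the last visit, and 8.3 lists safety in annual follow-up for five years. What is absent is the specific duty to report a pregnancy at once and follow it to outcome.

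**Conclusion.** The point holds for the body text. Contraception and pregnancy reporting end at nominal week 13, and the pause starts at week 17 or later, so no off-cART day is covered. The absence of pregnancy from the pause and restart criteria, and of any listed test after week 5, holds only if attachments J, M, X and AB do not supply them. It would be wrong to conclude that the trial has no pregnancy check after week 5. The week-9 criteria review is one, and the unseen schedule may hold others.

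The protocol does not give the number of women among the at most 24 participants; if none can become pregnant, the effect is nil. No endpoint, estimate or test is affected. This is a safety window set against the wrong event. It should be amended, but it is not a threat to the trial's conclusions.

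**What to change.** Check attachments J, M, N, X and AB first and align them with the body text. Then, for participants who pause:

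1. Extend the 7.2 contraception requirement and the 9.6 reporting and follow-to-outcome duty through cART resumption.
2. Name pregnancy in 7.3.3 as a reason not to start the pause, with a test strip at the existing week-17 visit if none is scheduled.
3. Name pregnancy in 8.1.15 as well as 8.1.16 as a reason to recommend restart at any pause visit, whatever the viral load. Section 8.1.16 alone is not enough, because that visit is reached only after a positive qualitative test. Add a strip at the pause visits that already include blood work (weeks 2, 4, 8 and 12, then monthly), so that a pregnancy beginning during the pause can be detected.

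Cost: amendment wording, a longer contraception requirement, and 1 + 4 = 5 strips per woman through pause week 12, then one a month. Strips are already listed in 8.4.2, and no new visits are needed.
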